**In a subgroup of patient *with* cardiogenic shock:**

- Improvement of hemodynamic parameters (CI, PCWP, and SVRI) from baseline to 24 and 48 hours.
- Number of days on intra-aortic-balloon counter pulsation treatment (IABP).
- Improvement of central venous oxygen saturation.
- Improvement of kidney function measured as creatinine clearance.
- Total mortality (number of patients alive at discharge).

**In patients *without* cardiogenic shock:**

- - The patient’s global assessment VAS-scale at 24 hours and at 5 days after the start of the study drug infusion.
  - Need for IV inotropes, at the clinicians decision, after start of the study drug infusion.

**Methods**

**Echocardiography**: Main endpoint in the study is improvement of regional contractility or wall motion score-index (WMSI). WMSI is measured by echocardiography including tissue Doppler imaging at baseline, 24 hours, 5 days and 6 weeks after the start of the study drug infusion.

**Blood analysis (see appendix II)**: A blood sample is frozen at baseline, after ending the infusion period, after 2 and 5 days and after 6 weeks after the start of the study drug infusion. BNP, haemostasis parameters and both pro- and anti-inflammation markers are analysed together at the end of the study in collaboration with [name] and [name] at Clinical Research Centre, Department of Heart-and Lung diseases, Ullevål University Hospital. Routine analyses like, troponin-T, lactate, creatinine, blood-gas analysis are done by the Department of Clinical Chemistry.

### Infarct size measurement

Infarct size will be assessed by technetium 99m-tetrofosmin myocardial SPECT (single photon emission computed tomography) imaging (8).

### Hemodynamic data

Hemodynamic data (cardiac index, cardiac power index, stroke volume, PCWP, SVRI, pulmonary artery pressure) and central venous oxygen saturation are collected by Swan-Ganz catheter. A Swan-Ganz catheter will only be used to monitor patients in cardiogenic shock.

The patient’s blood pressure will be monitored by non-invasive registrations except for patients in cardiogenic shock, which will be monitored, by invasive registrations.

**Assessment of symptoms and clinical findings:**

Global assessment is completed by the physician and the patient as change from baseline at 24 hours and at 5 days after the start of study drug treatment. A VAS-scale will be used to mark changes in symptoms. The physician will be asked to evaluate the degree of dyspnoea, respiratory frequencies, rales, third heart sound, hemodynamic assessment (cold/warm, clammy/dry extremities and urine output). Each patient will be scored on a scale from 1-4 describing the degree of symptoms. The patient will be evaluated again 24 hours after start of the study drug infusion. The patient is improved if the score is better and worsened if the score is worse. If the score is the same, the patient is unchanged. Worsening is defined as use of IV vasodilators, inotropic agents or IV diuretics. The patient will simply be asked to score symptoms on a VAS (1-10) scale at baseline, after 24 hours and 5 days.

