| **Methods** | - Regional contractility or wall motion score-index is measured by echocardiography including tissue doppler imaging at baseline and 24 hours, 5 days and 6 weeks after the start of the study drug infusion.   - Infarct size measured at 6 weeks by gated spect (radioisotope teqniche). - A blood sample is frozen at baseline and after 1, 2, and 5 days and after 6 weeks after the start of the study drug infusion. BNP, lactate and inflammation markers are analysed by methods specified in the study protocol. - Hemodynamic data (Cardiac index, stroke volume, PCWP, SVRI etc.) and central venous oxygen saturation are collected by a pulmonary artery-catheter (Swan-Ganz catheter) in a subgroup of patients in cardiogenic shock. - IV inotropes are allowed to be used freely in the subgroup of patients in cardiogenic shock, but not in the other patients. If IV inotropes is needed, the patient should be included in the cardiogenic shock subgroup. If IV inotropes is needed at the clinician’s decision after the start of the study drug infusion, this should be regarded as an endpoint. - Global assessment is completed by the physician and the patient as change from baseline at 24 hours and at 5 days after the start of study drug treatment. - ”Hospitalisation” is measured according to definitions in the study protocol and mortality and angiographic data is collected. - Safety variables (adverse events, HR, BP, ECG, lab, concomitant medication) are recorded during the study. - A prospectively defined subgroup of patients in cardiogenic shock will be randomised by stratified randomisation. |
| **Study medication** | Bolus dose of 12 ug/kg for 60 minutes. The bolus dose is followed by a continuous infusion of 0,1 ug/kg/min for 24 hours. Noradrenalin must be mixed and ready for use before starting the study drug infusion. If the dose is not well tolerated (systolic BP <80 mm Hg and a drop in MAP >10 mm Hg):  Reduce the dose to 0,05 ug/kg/min. If this is not sufficient:  Start noradrenalin infusion (start dose: 0.03 g/kg/min). If this is not sufficient: Stop the infusion of the study drug.  After 24 hours the infusion is turned off abruptly.  Placebo is administered in the same way as levosimendan. |
| **Total duration of study** | The study drug infusion is 25 hours long.  There are follow-up during the first 5 days and then at 6 weeks after the start of study drug treatment. The MACE end-point and total mortality will be measured at 6 weeks and at 6 months. |

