## Study protocol

**Patient group**

Patient with acute myocardial infarction referred to Ullevål University hospital.

**Major inclusion criteria:** Patients who are hospitalised with acute ST-segment elevation myocardial infarction (STEMI: ECG definition) subjected to acute PCI

*or*

patients with non-ST segment elevation myocardial infarction subjected to PCI within 72 hours after start of chest pain.

*and all of the following (1-3)*

- - Revascularization by PCI with opening of an occluded coronary artery or balloon dilatation of a stenotic coronary artery presumed to be culprit lesion
  - Depressed contractility of the left ventricle (left ventricle ejection fraction < 40 %) assessed by echocardiography
  - Dyspnoea at rest at screening and *at least* one of the following signs of left ventricular failure (within 48 hours after PCI):
    - Pulmonary edema
    - Signs of marked pulmonary congestion on chest x-ray
    - Need for continuous-elevated positive airway-pressure ventilation (CPAP) or mechanical ventilation
    - Need for IV diuretics.
    - Oliguria (<0.5 ml/kg/hour) as a sign of hypoperfusion of the kidneys after volume therapy.

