**Inclusion criteria**

Additional inclusion criteria includes *both* of the following:

- - Systolic BP <90 mmHg after 60 min of adequate volume therapy or systolic BP between 90 and 100 mmHg with inotropic support by catecholamine infusion
  - Signs of hypoperfusion (low-output heart failure)
    - Oliguria (diuresis <0.5 ml/kg/hour)
    - Cold, clammy extremities
    - Reduced consciousness

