**Primary endpoints**

**Efficacy parameters**:

- - Changes from baseline to 5 days in Wall motion score-index measured by echocardiography.
  - Changes from baseline to 5 days in BNP (Brain natriuretic peptide).
  - Clinical composite at 5 days after the start of the study drug infusion, according to the physician’s global assessment measured as change from baseline to 5 days.

**Safety parameters**: Number of patients developing:

- - Hypotension: BP < 90 mm Hg or a drop in mean arterial BP > 10 mm Hg in patients with cardiogenic shock.
  - Tachycardia (heart rate above 120).
  - Atrial fibrillation.
  - Ventricular arrhythmia (VT, VF, TDP).
  - Ischemic episodes (ECG changes or chest pain demanding treatment).

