**Concomitant treatment:**

All patients will be treated with acute PCI and standard medical therapy according to national and international guidelines on treatment of acute ST-elevation myocardial infarction. The use of IV inotropes is restricted to the subgroup in cardiogenic shock. An exception is the use of noradrenalin as rescue therapy as described below. There are no further restrictions in the use of medical treatment. If the responsible clinician decides that indications for the use of IV inotropes is present, this will be noted in the case report form as a study endpoint. In patients in cardiogenic shock, all medical treatment is allowed in addition to the study drug. The use of IV inotropes in all patients will be collected in the case report form.

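### The primary clinical composite is defined by two conflicting rules, so a patient can be both improved and worsened, and death before day 5 has no category

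*Protocol*

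**What the plan says.** The Protocol's list of primary efficacy parameters includes "Clinical composite at 5 days after the start of the study drug infusion", taken from the physician's global assessment. The only description of how patients are classed is under Assessment of symptoms and clinical findings, which holds two rules:

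- **Score rule.** The physician scores symptoms from 1 to 4 and the score is compared with baseline: "The patient is improved if the score is better and worsened if the score is worse". An equal score means unchanged.
- **Drug rule.** Shortly afterwards: "Worsening is defined as use of IV vasodilators, inotropic agents or IV diuretics".

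Four other parts of the Protocol bear on the drug rule:

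- Patient group lists "Need for IV diuretics" as one of five alternative signs of left ventricular failure, of which at least one is required.
- The additional inclusion criteria for the shock subgroup offer two alternative blood-pressure routes. One is "systolic BP between 90 and 100 mmHg with inotropic support by catecholamine infusion".
- The Methods row of the Protocol Summary says "If IV inotropes is needed, the patient should be included in the cardiogenic shock subgroup".
- Concomitant treatment says of shock patients: "In patients in cardiogenic shock, all medical treatment is allowed in addition to the study drug". For the others it restricts IV inotropes, with rescue noradrenalin as the exception, and then states "There are no further restrictions in the use of medical treatment".

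Death is named only in secondary endpoints: MACE, and mortality in the shock subgroup.

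**The concern.** The two rules can give opposite answers for one patient, and nothing says which prevails. The drug rule speaks of use. It does not require that the drug be started or increased after study drug begins, and it sets no time window. Treatment that a patient was already receiving at entry therefore meets it.

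Death is a separate gap. A patient who dies before day 5 has no day-5 score. The drug rule places that patient only if a listed drug happened to be given. The Statistics section makes all randomised patients the primary population for efficacy, so the definition cannot class everyone it has to cover.

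At stake is one of three primary efficacy results. It would depend on a choice between rules that the Protocol does not make. If the drug rule overrides the score, real changes in the score may be hidden.

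**Working it through.** **1. The rules side by side**

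| Patient at day 5 | Score rule | Drug rule |
| --- | --- | --- |
| Entered on an IV diuretic, still on it, score better | Improved | Worsened |
| In shock, entered on a catecholamine, still on it, score better | Improved | Worsened |
| Not in shock, score unchanged, inotrope newly needed | Unchanged | Worsened |
| Score better, noradrenalin given under the tolerance steps in Study medication | Improved | Worsened if noradrenalin counts as an inotrope; not stated |
| Died before day 5, no listed drug given | No score | Not met |

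The first two rows are contradictions over baseline therapy, and the last is a gap. The third needs only a precedence rule. Its drug-rule result agrees with the rest of the Protocol, which makes need for IV inotropes after the start of study drug an endpoint in patients without shock.

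The section also describes re-scoring only at 24 hours, although it plans the global assessment at both 24 hours and 5 days and the primary time point is 5 days.

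**2. What the Protocol's sizing covers**

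The sample size rests on WMSI alone: a difference of 0.2, SD 0.2, two-sided 0.05, power 0.80. The usual formula, 2 × (1.96 + 0.84)² × (0.2/0.2)², gives 15.7, so 16 per group. The stated 30 per group gives about 97% power for WMSI. No power is stated for the composite, so there is no figure of the plan to reproduce here.

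**3. Illustration of the effect on the composite**

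Assumptions, none of them from the Protocol: improved/unchanged/worsened by score is 40/40/20% on placebo and 70/20/10% on active. There are 30 patients per arm, compared by a two-sided rank-sum test at 0.05. A share f of an arm receives a listed drug, independently of score, and is overridden to worsened. Then:

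- improved = i(1 − f)
- unchanged = u(1 − f)
- worsened = w(1 − f) + f

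For f = 0.5 in both arms, placebo becomes 20/20/60% and active 35/10/55%. The only share with an anchor in the Protocol is the minimum number in shock, 14/60 = 23%. Using it assumes that exactly those patients are overridden. Power by simulation:

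| f placebo | f active | Power |
| --- | --- | --- |
| 0 | 0 | about 62% |
| 14/60 | 14/60 | about 29% |
| 50% | 50% | about 12% |
| 80% | 80% | about 6% |
| 50% | 30% | about 60% |
| 80% | 60% | about 47% |
| 80% | 50% | about 75% |

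A two-category version, assuming 35% versus 70% improved and equal f in both arms, gives 79% power at f = 0, 57% at 14/60 and 33% at 50%. The direction is the same and the size differs, so no single figure should be taken as the loss.

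**The case against.** **The drug rule may have been meant for rescue after baseline.** It sits in a paragraph about change from baseline, and the Protocol Summary treats inotropes needed after the start of study drug as the event. That reading is plausible, but the sentence does not say it, and it would still leave precedence and death open.

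**A reader might infer that most patients would be classed as worsened, so that the endpoint could not separate the arms.** The Protocol does not support this. Need for IV diuretics is one of five alternative signs, and inotropes at entry concern only the shock subgroup. The share on these drugs is not given. The steep loss of power also requires equal use in both arms, whereas the Protocol's hypothesis is that levosimendan could reduce the need for inotropes. With lower use on active drug, power was largely kept or even higher in some of the scenarios above.

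**A reader might also infer that counting inotropes as worsening is itself an error.** Outside shock it is not. Newly needed inotropes are an endpoint there, and the drug rule agrees with that.

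**WMSI is called the main endpoint and death is captured elsewhere.** Both are true, and they limit the damage to the trial as a whole. The composite is nevertheless listed as primary. An analysis plan could settle the matter only by choosing between rules that the Protocol leaves in conflict.

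**Conclusion.** The point holds as a defect in how a primary endpoint is defined. Two rules conflict, neither takes precedence, continued baseline therapy counts as worsening on the literal text, and death before day 5 has no category. None of this depends on assumed numbers.

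The size of the effect does. Under the assumed 40/40/20 versus 70/20/10 and an equal override in both arms, power falls from about 62% to about 29% at 14/60 and about 12% at 50%. If use is lower on active drug, the loss is smaller or absent, but the result then reflects drug use as much as the physician's score. The number of early deaths affected cannot be estimated from the Protocol.

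**What to change.** Reconcile the assessment section with the Methods row of the Protocol Summary, the inclusion criteria, Concomitant treatment and Study medication by stating one hierarchy, used at both 24 hours and day 5:

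1. **Worsened:** death before the assessment, a worse score than at baseline, or a listed IV drug newly started or increased after the start of study drug.
2. **Improved:** a better score and none of the above.
3. **Unchanged:** everyone else.

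Add that continued baseline therapy does not count. State whether noradrenalin given under the tolerance steps counts as worsening or is reported separately. State that the physician's score is repeated on day 5.

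This alters outcome classification only, not patient care. The cost is the endpoint wording and some data capture. The Protocol already records concomitant medication and inotrope use, but the case report form must also show when IV diuretics and vasodilators were started and whether they were increased.

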**Registration of hospitalisation and MACE:**

Days in CCI/ICU and total length of stay in hospital will be measured. In-hospital mortality will be measured. Time to death, non-fatal myocardial infarction or revascularization is measured at 6 weeks and 6 month. The Norwegian death registry will be used to compare mortality at 6 month.

**6 weeks control:**

All patients will receive a 6 weeks follow-up consultation, which will include physical examination by a physician, echocardiography, blood analysis and gated spect (radio-isotope technique) analysis of infarct size.

**Safety variables**:

Safety variables (adverse events, HR, BP, ECG, lab, concomitant medication) are recorded during the study with special emphasize on blood pressure, cardiac arrhythmias, ischemic episodes an concomitant use of other inotropic drugs. This will be monitored during infusion of study drug and during the next 5 days of follow-up.

**Concomitant treatment:**

All patients will be treated with acute PCI and standard medical therapy according to national and international guidelines on treatment of acute ST-elevation myocardial infarction. The use of IV inotropes is restricted to the subgroup in cardiogenic shock. An exception is the use of noradrenalin as rescue therapy as described below. There are no further restrictions in the use of medical treatment. If the responsible clinician decides that indications for the use of IV inotropes is present, this will be noted in the case report form as a study endpoint. In patients in cardiogenic shock, all medical treatment is allowed in addition to the study drug. The use of IV inotropes in all patients will be collected in the case report form.

**Study medication:**

A bolus dose of 12 ug/kg for 60 minutes. The bolus dose is followed by a continuous infusion of 0,1 ug/kg/min for 24 hours. After 24 hours the infusion is turned off abruptly. Placebo is administered in the same way as levosimendan.

Noradrenalin must be mixed and ready for use before starting the study drug infusion. This is important because some patients receiving levosimendan developvasodilatation and this is followed by a non-acceptable fall in blood pressure.

A non-acceptable fall in blood-pressure is defined as systolic BP below 80 mm Hg *and* a drop in mean arterial blood pressure > 10 mm Hg.

If the study drug is not well tolerated:

1. Decrease the infusion rate to 0,05 ug/kg/min. If this is not sufficient:
2. Start noradrenalin infusion (start dose: 0.03 g/kg/min). If this is not sufficient:
3. Stop the infusion of the study drug.

**Total duration of study:**

The study drug infusion time is 25 hours. There are follow-up evaluations during the first 5 days in hospital and then at 6 weeks after the start of study drug treatment. The MACE end-point and total mortality will be recorded at 6 weeks and at 6 months. Frozen blood samples will be stored (biobanking) for 15 years (-700C freezer) for potential further analyses.

**Number of patients:**

60 patients at Ullevål University hospital. A minimum of 14 patients in cardiogenic shock will be included. If necessary, the total number of patients in the study will be increased in order to reach the number of patients in cardiogenic shock.

**Statistics:**

The patients will be randomized and the data analyzed in collaboration with [name], PhD, at Center of Statistics, Ullevål University hospital.

*Determination of Sample Size:* The total number of 60 patients in the study is based on the following: WMSI as a marker of regional contractility is the main endpoint of the study. This index is higher in patients with increasing number of damaged segments of the left ventricle. We have evaluated the method in patients with myocardial infarction including patients given levosimendan infusion post-PCI.

We postulate, from our preliminary experience with levosimendan in this clinical setting, a reduction of WMSI from 1.6  0.2 (mean  SD) to 1.4  0.2 by adding levosimendan to standard therapy. This reduction represents a clinically important improvement of left-ventricular function. With = 0.05 (two-sided test) and 1- = 0.80, 30 patients in each group will be sufficient to detect a statistically significant difference between the groups.

*Randomization*: Patients meeting the entry criteria will be included in the study. A randomization code list will be computer generated by [name], PhD, at Centre of Statistics. Patients in the predefined subgroup “cardiogenic shock” will be randomized to this subgroup by stratified randomization. The randomization code list will be kept in a safe at the Hospital Pharmacy. In a medical emergency situation requiring knowledge of the identity of the study medication given to a patient, the Hospital Pharmacist that will be available on a 24-hour basis will open the randomisation code.

*Populations for Analysis:*

The principal analysis will be performed on an intention-to-treat principle. The intention-to-treat population includes all patients who were randomized to the active treatment arm and the placebo treatment arm whether or not they received the treatment. The intention-to-treat population is the primary population for all baseline and efficacy analysis. The as-treatment population includes all patients who actually received any amount of study drug. The as-treated population is the primary patient population for the safety analyses.

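### The protocol lists three unranked primary efficacy endpoints but elsewhere calls WMSI alone the main endpoint, and does not say which of them decides success

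*Protocol*

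**What the plan says.** The Primary endpoints section of the protocol lists three efficacy parameters. The imaging measure is given as "Changes from baseline to 5 days in Wall motion score-index measured by echocardiography". The second entry, a blood marker, reads "Changes from baseline to 5 days in BNP (Brain natriuretic peptide". The third, which rests on the physician's judgement, is the "Clinical composite at 5 days after the start of the study drug infusion". They are not ranked. Five safety counts follow under the same heading, in a separate safety sub-list. The Protocol Summary repeats the whole list, although its row label is in the singular.

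Two other places single out WMSI. Methods, under Echocardiography, says "Main endpoint in the study is improvement of regional contractility or wall motion score-index (WMSI". Statistics, under Determination of Sample Size, says "WMSI as a marker of regional contractility is the main endpoint of the study" and bases the 60 patients on it: WMSI 1.6 against 1.4, SD 0.2, two-sided alpha 0.05, power 0.80, 30 per group. This is the only alpha in the protocol. None is given for BNP or the composite, and no rule combines the three results.

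**The concern.** A reader who starts from the endpoint list sees three primary efficacy endpoints. A reader who starts from the sample size sees one. The two readings allow different conclusions from the same data. With a null WMSI and a significant BNP or composite, the first reader may report a met primary endpoint, while the second must report a trial that missed its main endpoint.

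Neither statement can be used without the other. The two places that call WMSI the main endpoint give it no time point, and Methods schedules follow-up echocardiography at 24 hours, 5 days and 6 weeks. Only the primary list fixes day 5. To learn when the main endpoint is assessed, one has to go to the list that also makes BNP and the composite primary.

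**Working it through.** **1. The plan's own figure.** Inputs from Determination of Sample Size: difference 1.6 − 1.4 = 0.2, SD 0.2 (standardised difference 1.0), two-sided alpha 0.05, power 0.80. By the normal approximation, n per group = 2 × (1.960 + 0.842)² / 1.0² = 15.7, so 16 (17 by t-test). The stated 30 per group is not reproduced, but it is more than sufficient: it gives 97% power on these inputs. The calculation concerns WMSI only, and the protocol gives no inputs for BNP or the composite.

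**2. False-positive risk under each possible success rule.** Assumption where more than one test counts: each is run at two-sided 0.05, a level the protocol states only for WMSI.

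| Rule | Chance of at least one false-positive result |
|---|---|
| WMSI alone decides | 5% |
| All three must succeed | at most 5% |
| Any one of three, independent | 1 − 0.95³ = 14.3% |
| Any one of three, pairwise correlation 0.3 | 13.6% |
| Any one of three, pairwise correlation 0.5 | 12.5% |
| Any one of three, pairwise correlation 0.7 | 10.9% |
| Any one of three, pairwise correlation 0.9 | 8.4% |
| Any one of three, any dependence | at most 3 × 0.05 = 15% |

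The rows with correlation come from simulating three equally correlated normal test statistics (2,000,000 draws each). The protocol gives no correlations, so these are a range and not an estimate. These figures count false findings in either direction. Counting only those that favour levosimendan, the any-one-of-three figure under independence is 1 − 0.975³ = 7.3%, against 2.5% for a single endpoint.

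**3. What it would cost to keep all three primary.** Splitting 0.05 equally gives 0.05 / 3 = 0.0167 per test. For WMSI on the stated inputs, n per group = 2 × (2.394 + 0.842)² = 20.9, so 21 (23 by t-test), and 30 per group gives about 92% power by t-test (93% by normal approximation).

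That result depends on the SD. The sample-size means read as WMSI levels, while the endpoint is change from baseline. With equal SDs at both visits, the SD of change is 0.2 × √(2(1 − ρ)), where ρ is the correlation between baseline and day 5. It is 0.2 if ρ = 0.5 and 0.28 if ρ = 0. The protocol does not give ρ. At the assumed SD of 0.28, alpha 0.0167 would require 42 per group, and 30 per group would give about 61% power by t-test. At alpha 0.05, the same SD leaves about 77%.

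**The case against.** The best defence is that the protocol already points to WMSI. It comes first in both lists, is called the main endpoint in two sections, and is the only endpoint with an alpha, an effect size and a power. Main among the primary endpoints can be read as a ranking, and on that reading the confirmatory error is 5%. The order of testing and the multiplicity method may also sit in the SAP, which was not available here.

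Much of this stands. It rules out saying that the plan's error rate is 14%. A reader might infer that from the three-item list, but it needs an any-one-of-three rule that the protocol never states, two further tests at 0.05 that it does not specify, and independence. The defence also limits what should be criticised: leaving test mechanics to the SAP is normal.

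It does not remove the inconsistency. Which endpoint is primary is a protocol decision, and this protocol makes it in two different ways. Calling WMSI the main endpoint does not take the primary label off BNP and the composite.

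A reader might also pool the five safety counts with the three efficacy endpoints and quote 1 − 0.95⁸ = 33.7%. The documents do not support that. The safety items are numbers of patients with events, no test or alpha is stated for them, they have their own sub-heading, and Populations for Analysis assigns safety to the as-treated population. A chance safety difference is not a route to an efficacy claim.

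**Conclusion.** The point holds as an inconsistency about which endpoint decides the trial. The protocol favours WMSI but does not say that WMSI alone is confirmatory, so a success claim resting on BNP or the composite remains open.

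The size is conditional. There is no inflation if WMSI alone decides or if all three must succeed. If all three are required, power also depends on BNP and the composite and cannot be computed from the protocol. If any one suffices at two-sided 0.05, the error is two to three times the stated level over the correlation range 0.7 to 0. Nothing shows that the sponsor intends that rule; the fault is that the text permits it. Because this governs the headline conclusion of a phase III trial and can be settled by wording, it should be settled before unblinding.

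**What to change.** In the Protocol Summary, Primary endpoints, Methods (Echocardiography) and Statistics, name change in WMSI from baseline to day 5 as the single primary efficacy endpoint, tested at two-sided 0.05. Make BNP and the clinical composite secondary, or test them in a prespecified fixed order only after WMSI succeeds. The protocol does not rank those two, so the order is the sponsor's choice. Add a sentence saying that the five safety counts are not part of the efficacy success rule.

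This follows the sponsor's own sizing and needs no extra patients. The cost is that neither BNP nor the composite can carry the trial alone at 0.05.

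If all three must stay primary with any one sufficient, state that rule and control the error by Bonferroni (0.0167 each) or Holm (0.0167, then 0.025, then 0.05 in order of the p-values). Before choosing this, the sponsor should establish the SD of change in WMSI and supply planning inputs for BNP and the composite, since the power cost for those two is unknown.

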**Scientific value-summarized**

The present study will provide new knowledge about the effects and safety of levosimendan in the clinical setting of acute myocardial infarction complicated by left ventricular failure in spite of modern rreperfusion therapy by acute PCI.

The study will provide new information about whether increasing the calcium sensitivity of the myofilaments and vasodilatation could improve regional contractility during the stunning period after restoriation of epicardial blood flow by PCI. The double blind, placebo controlled design makes it possible to study the effect of the active study drug on regional contractility during a time period with expected improvement of contractility in the hours after PCI due to gradually reduced stunning.

The study will contribute to already existing information about the safety of levosimendan during acute myocardial infarction with special emphasis on cardiac arrythmias, hypotension and new ischaemic episodes.

The study will provide new information about the effect of levosimendan on inflammation which has been proposed to be an important part of the stunning mechanism.

The study will gain knowledge on the use of levosimendan in patients with cardiogenic shock. This is a group of patients which is almost always excluded from clinical trials and lack of information about pharmacological treatment is striking. We (see Appenix) and others (7) have used levosimendan in this setting as add-on therapy to catecholamines, but this should be done as a part of a placebo-controlled trial. Although the expected numer of patients in cardiogenic shock in the present trial is too low to provide information regarding mortality, the study will nevertheless give information about the effects of levosimendan on regional contractility, hemodynamics, potential side-effcts and the practical approach of combining levosimendan and catecholamines.

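### The stated WMSI assumptions give 17 patients per group for 80% power, not 30; either the power or the SD in the sample-size paragraph is misstated

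*Protocol*

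**What the plan says.** Under Statistics, Determination of Sample Size, the protocol attributes the total of 60 to a single calculation and says that "WMSI as a marker of regional contractility is the main endpoint of the study". It postulates "a reduction of WMSI from 1.6" (SD 0.2) to 1.4 with an SD of "0.2 by adding levosimendan to standard therapy". Alpha is 0.05, two-sided. The conclusion attaches the group size directly to a power of 0.80: "30 patients in each group will be sufficient to detect a statistically significant difference between the groups". The plus-minus, alpha and beta symbols are lost in the text as read, but the meaning is clear and the loss is not a fault of the plan.

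Under Primary endpoints, the WMSI endpoint is "Changes from baseline to 5 days in Wall motion score-index measured by echocardiography". The sample-size paragraph gives no SD for that change and no correlation between baseline and day 5. It also states no allowance for dropout, for multiple primary endpoints or for a rank test.

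The section Number of patients sets a minimum of 14 patients in cardiogenic shock and lets the total rise to reach it. It does not derive the 60 from that minimum.

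**The concern.** A difference of 0.2 with an SD of 0.2 is a full standard deviation, and detecting that with 80% power takes far fewer than 30 patients per group. So the four elements of the statement (difference, SD, power and size) cannot all be right together. Either the power belonging to 30 per group is not 80%, or the calculation used an SD that is not the one printed.

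This matters because the paragraph is the stated basis for the 60 patients and concerns the main endpoint. A reader cannot tell from it which difference the trial was sized to detect. When the results are reported, the observed SD and confidence interval will be set against a planning statement that does not hold as written.

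**Working it through.** **Inputs** (all from Determination of Sample Size): means 1.6 and 1.4, so the difference is 0.2; SD 0.2 in each group; two-sided alpha 0.05; power 0.80; equal groups of 30.

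**Step 1. Attempt to reproduce the 30.** Normal approximation:

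n per group = 2 × (1.96 + 0.842)² × (SD / difference)² = 2 × 7.85 × (0.2 / 0.2)² = 15.7, so 16.

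The exact t-test calculation gives 16.7, so 17 per group (34 in total). Power is 78.1% at 16 and 80.7% at 17. The plan's 30 is not reproduced.

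**Step 2. Power at 30 per group.** Normal approximation: 0.2 / (0.2 × √(2/30)) − 1.96 = 3.873 − 1.960 = 1.913, which gives 97.2%. The t-test gives 96.8%.

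**Step 3. What 30 per group detects with 80% power.** By t-test the detectable standardised difference is 0.736. With SD 0.2 that is 0.736 × 0.2 = 0.147 WMSI units. For a difference of 0.2, the SD would have to be 0.2 / 0.736 = 0.272.

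**Step 4. Do ordinary variants bridge the gap?** With difference 0.2 and SD 0.2 kept:

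| Variant | Per group |
| --- | --- |
| One-sided test (normal approximation) | 13 |
| 90% power (t-test) | 23 |
| 95% power (t-test) | 27 |
| Alpha 0.05/3 for three primary efficacy endpoints (t-test) | 23 |
| Rank-test inflation of 17 | 18 to 20 |
| Dropout needed to turn 17 into 30 | about 43%, since 17 / (1 − 0.43) = 29.8 |

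None of these allowances is stated, and none of ordinary size reaches 30.

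**Step 5. Level SD versus change SD.** The printed SDs belong to WMSI levels, but the endpoint is a change. If 0.2 is the SD at each time point and r is the baseline/day-5 correlation, then SD of change = 0.2 × √(2(1 − r)).

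- r = 0.1: SD 0.268. The t-test needs 29.2, so 30 per group, and power at 30 is 81.0%.
- r = 0.5: SD 0.200, which returns to 17 per group.

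The SD of 0.272 from step 3 corresponds to r = 1 − (0.272 / 0.2)² / 2 = 0.08. So 30 per group at 80% power is what an unadjusted change-score calculation gives with a correlation of about 0.1. The protocol states neither that correlation nor the resulting SD; r is an assumption here.

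**The case against.** The strongest reply is that the protocol says only that 30 per group will be sufficient. On its own inputs that is true, because 30 exceeds 17. The mismatch is in the safe direction, and reading the trial as having 80% power for 0.2 understates its power on those inputs. This stands, and it limits the seriousness of the point. It does not remove it, since the text ties the 30 to a power of 0.80 and says that the total is based on these figures.

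A second reply is that step 5 may be what was done, in which case the calculation is sound and only an input is missing. That is possible, and the documents cannot decide it. But the printed SD would then not be the one used, so the paragraph would still need correcting.

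Two stronger readings are tempting and are not supported:

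- *The trial is underpowered because a change has a larger SD than a level.* This holds only if the correlation is low and change is analysed without baseline adjustment. The protocol gives no correlation. With adjustment, the residual SD is 0.2 × √(1 − r²), which is never above 0.2, so power at 30 per group would be about 97% or more. The analysis model may properly be left to the SAP.
- *The 0.2 includes recovery that placebo patients would share.* The section Scientific value-summarized does expect "a time period with expected improvement of contractility in the hours after PCI due to gradually reduced stunning", and the 0.2 comes from preliminary experience with levosimendan. But the sample-size paragraph ascribes the reduction to adding levosimendan to standard therapy and speaks of a difference between groups. Its natural reading is a between-group contrast. No figure in the document says how much of the 0.2 could be shared recovery, so no loss of power can be calculated.

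**Conclusion.** The sample-size statement is wrong as written. On the stated inputs, 80% power needs 17 per group by t-test (16 by normal approximation). Thirty per group gives about 97% power for 0.2, or 80% power for 0.147. These results assume a two-sample comparison of means with equal groups and the printed SD as the SD of the analysed quantity. The stated size and power fit together for a difference of 0.2 only if that SD is about 0.27, which the protocol does not say.

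The fault is minor to moderate. It is one of consistency and traceability, it errs on the safe side on the stated inputs, and it gives no ground for either reducing or enlarging the trial. Whether the power or the SD is the misstated element cannot be settled from the protocol.

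**What to change.** Keep 60 patients and correct the paragraph so that difference, SD, power and size agree. The sponsor should check which SD the calculation used and then do one of the following:

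- If 0.2 is the SD of the quantity to be analysed, restate the power: 30 per group gives about 97% power for a difference of 0.2, or 80% power for a difference of 0.147.
- If another SD was used, such as an SD of the day-5 change near 0.27, print it in place of 0.2, say that it is the SD of the change, and keep 80%.

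In either case, name the quantity to which the SD refers. If some other allowance produced the 30, state it. The cost is one reworded paragraph, with no extra patients and no change to the conduct of the trial.
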